## Discussion

3

While intrahepatic cholestasis of pregnancy is widely recognized for its association with preterm birth and fetal complications, a growing body of evidence suggests that neonatal respiratory morbidity may arise independently of gestational age. Clinical case series have proposed that elevated bile acids may directly compromise pulmonary adaptation in affected neonates through mechanisms consistent with bile acid-induced chemical pneumonitis (6). Zecca et al. reported severe respiratory distress in late preterm and early-term infants born to mothers with ICP, despite clinical indicators of lung maturity. The detection of bile acids in bronchoalveolar lavage fluid and the rapid response to surfactant therapy support the hypothesis that bile acid exposure may generate a qualitative surfactant deficit at birth, a pathway that has also been reinforced by animal studies (4, 9–11). More recently, experimental and translational studies have demonstrated that bile acids can impair surfactant synthesis, destabilize the alveolar epithelium and activate inflammatory cascades that hinder postnatal lung adaptation, lending further weight to the concept of bile acid-mediated respiratory injury as a distinct perinatal entity (12–14).

Despite this growing theoretical framework, prospective human data quantifying the extent of pulmonary compromise in neonates exposed to ICP remain scarce. No standardized approach currently exists to assess whether bile acid exposure at clinically relevant concentrations results in measurable surfactant dysfunction or biochemical evidence of lung injury at birth. The CHOLE-RESP study was designed to address this critical knowledge gap. Its prospective design, rigorous matching of controls by gestational age, birthweight, and sex, and integration of both clinical outcomes and serum biomarker analysis represent a structured and comprehensive approach to investigating this emerging hypothesis.

Several design features strengthen the internal validity and feasibility of this study. By including both term and preterm neonates, the study captures the full clinical spectrum of ICP-related deliveries and enables stratified analyses. Also, given the multifactorial nature of neonatal respiratory distress syndrome, statistical models incorporate established clinical risk factors, including gestational age, sex and perinatal infection, to minimize residual confounding and avoid overestimation of the effect of bile acid exposure. Biological samples are collected at defined time points and handled according to standardized protocols, with laboratory personnel blinded to group allocation. The decision to integrate all sampling into clinically indicated procedures minimizes patient risk and reinforces ethical compliance.

Additionally, preliminary retrospective data from our center (June 2020 to December 2024) identified 66 preterm infants born to mothers with ICP among 1,078 preterm births. Although the overall incidence of RDS was not consistently increased, these neonates demonstrated greater respiratory morbidity, with higher requirements for invasive ventilation, non-invasive CPAP and surfactant, as well as longer duration of respiratory support compared with controls. It should be noted that the relatively low number of ICP cases observed retrospectively reflects previous limitations in clinical practice, as bile acid testing was not routinely performed in Romania and often not covered by the public health system. Since October 2024, however, systematic testing for symptomatic mothers and updated obstetric management have been implemented in our institution, already resulting in 54 ICP-exposed neonates recruited within 14 months of prospective enrollment, confirming the feasibility of the study, with control recruitment scheduled to begin after one year. Technical validation of the ELISA kits has been performed in advance and preliminary biomarker analysis will commence once 60 participants are enrolled, with interim results expected to be presented at an international neonatology conference.

Nevertheless, certain limitations are anticipated. As a single-center study, generalizability may be limited, though the use of carefully matched controls mitigates this to some extent. Practical constraints may occasionally lead to delays in sample centrifugation, in which case samples will be stored at 2–5 °C in a dedicated medical-grade refrigerator. Sample hemolysis or insufficient serum volume may affect the ability to test all biomarkers, however these deviations will be documented transparently and addressed in the final analysis. Although early neonatal death is expected to be rare, it may act as a competing risk for outcomes such as RDS. Therefore, all mortality events and their timing will be recorded and considered in the interpretation of respiratory outcomes.

Ethical considerations have been fully integrated into the study design. Informed consent is obtained only after obstetric teams confirm an imminent delivery and before administration of anesthesia. Mothers are given time and autonomy to ask questions and are clearly informed of their right to decline or withdraw participation, without any impact on neonatal care. Blood samples are collected exclusively during procedures already indicated for clinical care, otherwise, if no clinical indication exists or the neonate's condition prohibits collection during a designated window, the sample is skipped and the reason will be included in the study's final reporting.

The CHOLE-RESP study has the potential to significantly advance the field by providing the first structured clinical and biochemical assessment of neonatal respiratory outcomes following ICP exposure. If the study confirms a measurable link between bile acid exposure and pulmonary injury, this could support the development of risk-based screening tools and tailored respiratory management strategies. Moreover, growing evidence from metabolomic and proteomic research suggests that intrahepatic cholestasis of pregnancy is associated with complex molecular signatures extending beyond bile acid concentrations alone (15, 16). Within this framework, the present study lays the groundwork for future multicenter validation efforts, broader biomarker profiling and the integration of hypothesis-generating omics approaches aimed at refining risk stratification and improving outcomes in this understudied neonatal population.

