### Study design

2.1

This is a single-center, prospective cohort study conducted in the Neonatology Department of the “[name]. Panait Sîrbu” Clinical Hospital of Obstetrics and Gynecology in Bucharest, Romania. The study initiated enrolment on October 1st 2024 and is expected to complete recruitment by December 31st 2027, after which follow-up and data analysis will be conducted.

Eligible study participants (neonates born at term or preterm age), enrolled by invitation, will be recruited following the provision of written informed consent by the legal guardian (the mother). The rights and welfare of all participants will be protected in accordance with the principles outlined in the Declaration of Helsinki.

A SPIRIT schedule and overview of the study design can be found in Figures 1, 2.

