### Eligibility criteria

2.4

Participants will be enrolled into either the exposed or unexposed group based on predefined eligibility criteria. The exposed group will consist of neonates born to mothers with a recent diagnosis of intrahepatic cholestasis of pregnancy, defined by serum bile acid concentrations exceeding 10 µmol/L within seven days prior to delivery. Furthermore, written informed consent needs to be obtained at least one hour prior to birth. No minimum gestational age at delivery is imposed and eligible neonates must be either born at the study location or transferred to the unit from another neonatal facility within the first 24 h of life. Exclusion from this group will apply in instances where informed consent is not provided, where no serum bile acid measurement is available in the specified time frame or where measured bile acid levels are below 10 µmol/L.

The unexposed group will comprise neonates born at the same institution to mothers without a known history of hepatic disease prior to or during the index pregnancy. Controls will be matched according to gestational age at birth, birthweight and sex. Consistent with the ICP-exposed group, informed consent must be obtained a few hours before delivery. Maternal administration of ursodeoxycholic acid at any point during pregnancy, regardless of dosage or timing, will constitute an exclusion criterion for this group, as it may suggest subclinical hepatic dysfunction.

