### Sample processing

2.6

Following blood collection, samples will be immediately transported to the central laboratory for processing. Centrifugation will be performed using an Orto Alresa Microcen 23 centrifuge, operated at 4,000 revolutions per minute (rpm) for 10 min, under room temperature conditions. After centrifugation, the separated serum will be transferred into a single, pre-labeled Eppendorf tube for each participant. All samples will be stored at −50 °C until further analysis. No aliquoting will be performed and all samples will remain under uniform storage conditions throughout the study duration to minimize pre-analytical variability. Upon completion of recruitment, stored serum samples will undergo batch analysis to quantify selected biomarkers associated with surfactant deficiency and pulmonary injury. Quantitative evaluation will be conducted using commercially available sandwich enzyme-linked immunosorbent assay (ELISA) kits validated for use in human serum. To safeguard the novelty of this research, the specific biomarkers evaluated will be disclosed following validation and publication of study findings.

To ensure participant anonymity and maintain blinding during laboratory analyses, each sample will be labeled using a unique alphanumeric code. The coding format will be as follows: “CS” for neonates born to mothers with cholestasis or “FC” for those born to mothers without liver disease, followed by the first initial of the neonate's last name, an optional number for multiple births (1, 2, or 3 for twin or triplet order), a gender identifier (5 for male, 6 for female), and the date of birth in the format DDMM. For example, a male neonate, twin 1, born to a mother with cholestasis, with the last name Niculae, and born on 21st of May, would be assigned the code CSN152105. This code will be recorded on both the primary collection tube and the Eppendorf storage tube. The code list will be securely maintained by the principal investigator, and laboratory personnel responsible for biomarker analysis will remain blinded to the clinical identity and group assignment of each participant.

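### Controls start a year after exposed neonates and are not matched on birth date, so exposure is partly confounded with calendar period and, for the biomarkers, with serum storage time or assay batch

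*Protocol article*

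**What the plan says.** - **Timing.** Study design (2.1): "The study initiated enrolment on October 1st 2024 and is expected to complete recruitment by December 31st 2027". The Discussion reports systematic bile acid testing since October 2024, "already resulting in 54 ICP-exposed neonates recruited within 14 months of prospective enrollment", "with control recruitment scheduled to begin after one year". The date from which that year runs is not stated, and at 14 months control recruitment is still described as scheduled.
- **Matching.** Eligibility criteria (2.4): "Controls will be matched according to gestational age at birth, birthweight and sex". Birth date is not a factor.
- **Covariates.** Statistical analysis (2.8) names gestational age. The Discussion adds sex and perinatal infection. Neither names enrolment date or storage time.
- **Assay.** Sample processing (2.6): "Upon completion of recruitment, stored serum samples will undergo batch analysis", after storage at −50 °C, and "all samples will remain under uniform storage conditions throughout the study duration to minimize pre-analytical variability". The Discussion, however, starts a preliminary biomarker analysis once 60 participants are enrolled.
- **Limitations.** The Discussion mentions delayed centrifugation, haemolysis and short sample volume, but neither the control lag nor storage duration.

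**The concern.** If serum waits in the freezer until recruitment closes, an earlier birth means an older sample. Exposed neonates are born earlier on average, so their sera are older. Uniform conditions hold the temperature constant, not the duration. Any change of the analyte in storage then becomes part of the estimated ICP effect on the biomarkers, which the protocol calls a central component of the design and for which it chose 0.95 power.

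If the first 60 participants are assayed early instead, most of them will be exposed, and the imbalance moves from storage time to assay batch.

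RDS and surfactant use are not affected by storage. They depend partly on clinical decisions, so a drift in practice over the recruitment period could enter those comparisons. Exposed neonates from the first year have no contemporaneous controls, and later modelling can only partly make up for that.

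**Working it through.** **1. The plan's own figure.** Inputs from Sample size calculation (2.3): one-sided α 0.05, d = 0.5, 66 exposed and 132 unexposed. Noncentrality = 0.5/√(1/66 + 1/132) = 0.5 × √44 = 3.32 on 196 degrees of freedom; power 0.952. With 65 and 130 it is 0.949. The stated sample size is correct for the unadjusted comparison.

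**2. Accrual.** The rate is 54/14 = 3.86 per month. In 12 months that gives 12 × 3.86 = 46 exposed, which is 70% of 66. The 66th arrives at 66/3.86 = month 17.1. The window from 1 October 2024 to 31 December 2027 is 39.0 months. Controls are taken to start at month 12.

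**3. Gap in mean birth date, which is also the gap in mean storage time under a single final batch.**

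| Scenario | Exposed, months | Controls, months | Mean birth month | Gap | Exposed before any control |
|---|---|---|---|---|---|
| A: exposed stop at 66, controls to the close | 0–17.1 | 12–39 | 8.6 vs 25.5 | 16.9 | 70% |
| B: exposed stop at 66, controls at twice the exposed rate | 0–17.1 | 12–29.1 | 8.6 vs 20.6 | 12.0 | 70% |
| C: exposed spread evenly over the window | 0–39 | 12–39 | 19.5 vs 25.5 | 6.0 | 31% (12/39.0) |

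In A, (39.0 − 17.1)/(39.0 − 12) = 81% of controls come after the last exposed neonate. C is stylised: with 54 already enrolled, 66 can no longer be spread evenly. At the reported rate the full window would yield 3.86 × 39.0 = 150 exposed, and 46/150 is the same 31%.

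**4. Storage bias.** The documents give no stability figure and do not disclose the biomarkers, so both inputs are assumptions: 5% loss per year and a log-scale SD of 0.5. Bias in SD = ln(0.95) × (gap/12)/0.5. Power and type I error come from the noncentral t with 66 and 132, one-sided.

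| Gap (months) | Bias (SD) | Power at d = 0.5 | Type I error if the shift has the opposite sign |
|---|---|---|---|
| 6 | −0.05 | 0.91 | 0.10 |
| 12 | −0.10 | 0.84 | 0.17 |
| 16.9 | −0.145 | 0.76 | 0.25 |

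Over 2–10% change per year, log-SD 0.5–0.7 and gaps of 6–17 months, the shift ranges from about 0.01 to 0.30 SD in absolute size.

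**5. What adjustment costs.** With enrolment date as a linear covariate, the variance of the group effect is inflated by 1/(1 − r²), where r is the correlation of group with enrolment date. In A and B, r ≈ −0.75, inflation is 2.29 and power is about 0.70. In C with 66 exposed, r ≈ −0.29, inflation is 1.09 and power is about 0.93. Dropping exposed neonates born before month 12 leaves 66 − 46 = 20 against 132 controls in A (power 0.67, at best, since this still counts the controls born after month 17). In C it leaves about 46 against 132 (power 0.90).

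**6. The analysis at 60.** Exposed neonates alone would reach 60 at 60/3.86 = month 15.6. If controls start at month 12, 46 of the first 60 are already exposed. So between 46 and 60 of those 60 (77–100%) would be exposed.

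**The case against.** The strongest defence has five parts.

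- **Practice change.** A reader might infer that exposure is confounded with changed obstetric practice, because the Discussion says "Since October 2024, however, systematic testing for symptomatic mothers and updated obstetric management have been implemented in our institution". The documents do not support that. The change dates from the month in which exposed enrolment began, so both groups follow it. It separates the prospective cohort from the 2020–2024 retrospective data, not exposed from control. No later change in practice is described. This objection stands in full.
- **Overlap.** 66 and 198 are minimums and recruitment is open to December 2027, so the groups can overlap from month 12. This stands, and is why the 6-month case belongs in the range. It does not remove the imbalance: in that case 31% of exposed neonates still precede any control.
- **Direction.** A reader might infer that storage loss would manufacture a positive finding. On the planned one-sided test, loss lowers the older exposed values and runs against the hypothesis: at −0.145 SD type I error is about 0.005, and the harm is lost power. Only a shift in the other direction inflates false positives, and neither direction is documented.
- **Assay timing.** The analysis at 60 participants may mean that early sera are not stored to the end. This stands as a conflict between the Discussion and Sample processing, but it replaces a storage imbalance with a batch imbalance.
- **Analysis detail.** The Discussion's covariate list is open-ended, and plate layout or sensitivity analyses may sit in a document not shown. That is fair for the analysis. The lag and the matching factors are design choices fixed in this article.

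**Conclusion.** The point holds as partial confounding. Following the plan as written ties exposure to birth period and, for the biomarker objective, to serum age or assay batch, and nothing named in matching, covariates or limitations addresses it. About 46 exposed neonates precede any control, with a mean gap of 12–17 months if exposed enrolment stops at 66 and about 6 months if it spans the window. These figures assume constant accrual and a control start at month 12. As controls were still described as scheduled at month 14, the lag may be longer.

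The power loss and the type I error range rest on assumed analyte loss and variability. They show what is plausible and are not estimates for these biomarkers. For RDS and surfactant use no mechanism beyond possible calendar drift is documented and no size can be given, so it would be wrong to say that all three co-primary objectives are shown to be biased.

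**What to change.** 1. Enrol controls concurrently from now on. Add birth date (for example ±4 weeks) as a matching factor for every exposed neonate enrolled from now on, and state the control start date.
2. Keep exposed enrolment open alongside controls to the planned December 2027 close instead of stopping at 66.
3. Assay each exposed neonate and its matched controls on the same plate. Reconcile the analysis at 60 participants with the end-of-recruitment batch.
4. Record months in storage. Pre-specify one sensitivity analysis adjusted for enrolment date or storage time, and one restricted to the concurrent period.
5. List the control lag and storage duration among the limitations.

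**Cost.** Matching becomes harder. With 66 exposed in total, the adjusted and concurrent-only analyses have less than the stated 0.95 power: about 0.93 and 0.90 if exposed enrolment is spread over the window, about 0.70 and 0.67 if it stops at month 17. The protocol should say so. Continued enrolment recovers this: at the reported rate, 150 − 46 = 104 exposed would be born after month 12, and 104 against 132 controls gives a noncentrality of 0.5/√(1/104 + 1/132) = 3.81 and power of about 0.98. The 66/132 calculation for the unadjusted comparison needs no change.

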## Ethics and dissemination

4

The CHOLE-RESP study protocol received approval from the Ethics Committee of the “[name]. Panait Sîrbu” Clinical Hospital of Obstetrics and Gynecology (Approval No. 34/15.10.2024) and was registered on ClinicalTrials.gov (NCT06679972).

Written informed consent is obtained from the legal guardians of all participants after the obstetric team confirms the likelihood of delivery within the next 24 h and prior to the administration of anesthesia. Mothers are fully informed of the study objectives and procedures, and reassured of their right to decline or withdraw participation at any point without consequences to the medical care provided to their newborn.

Biological samples are collected only during routine clinical blood draws to minimize patient discomfort. In cases where the clinical condition of the neonate precludes timely collection, sampling is deferred to the next scheduled blood test within the collection window. Deviations from the planned sampling protocol, such as refrigeration of unprocessed samples or collection of hemolysed or insufficient serum, are documented and will be transparently addressed in the final manuscript.

Study findings will be disseminated through presentations at scientific conferences and submitted for publication in peer-reviewed journals. Preliminary results will be shared upon completion of the initial recruitment target. No personal identifying information will be published, and all data will be anonymized prior to dissemination.

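### The Discussion starts biomarker assays at 60 participants, section 2.6 waits until recruitment ends; an early run would be about 90% exposed and would tie assay run or an extra thaw to exposure

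*Protocol article*

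**What the plan says.** Section 2.6 (Sample processing) sets the assay schedule: "Upon completion of recruitment, stored serum samples will undergo batch analysis to quantify selected biomarkers associated with surfactant deficiency and pulmonary injury". On storage it says that "the separated serum will be transferred into a single, pre-labeled Eppendorf tube for each participant", and adds: "No aliquoting will be performed and all samples will remain under uniform storage conditions throughout the study duration to minimize pre-analytical variability".

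The Discussion (section 3) gives a different schedule: "preliminary biomarker analysis will commence once 60 participants are enrolled, with interim results expected to be presented at an international neonatology conference". The same paragraph reports recruitment to date, "already resulting in 54 ICP-exposed neonates recruited within 14 months of prospective enrollment", and states that controls were to be recruited only from one year onward. It does not say how many controls have been enrolled.

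Ethics and dissemination (section 4) has a further trigger for early release: "Preliminary results will be shared upon completion of the initial recruitment target". That target is not defined. It may or may not be the 60 of the Discussion.

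Section 2.3 calls the biomarker differences a novel co-primary objective and sizes the study on them. Section 2.8 compares groups by t-test or Mann–Whitney test at each time point. It names gestational age as an added covariate and mentions no term for assay run.

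**The concern.** Waiting until recruitment ends and assaying everything then is sound: exposed and control samples can share plates, kit lots and thaw history. An assay at 60 participants breaks this, and the order of recruitment makes the break uneven. Exposed infants came first and controls a year later, so an early run takes most of the exposed group and almost none of the controls.

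The article does not say what becomes of the early values. There are three possibilities, each with a cost:

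- **Keep them.** Any shift between the early run and later runs then enters the comparison of exposed with unexposed infants.
- **Re-assay the same tubes at the end.** Run is then balanced, but with no aliquots the extra freeze-thaw cycle falls almost only on exposed samples.
- **Discard those infants' biomarker data.** This removes up to 54 of the 66 exposed infants that the sample size requires.

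The first two are mainly alternatives; their effects should not be added together. A thaw cannot be reversed, and with 54 exposed infants enrolled the trigger is close.

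**Working it through.** **1. The plan's own figure.** Section 2.3: one-sided two-sample t-test, d = 0.5, alpha 0.05, 66 exposed and 132 unexposed. The noncentrality is d × √(66 × 132 / 198) = 0.5 × √44 = 0.5 × 6.633 = 3.317 on 196 degrees of freedom. Power is 0.9516, against the stated 0.952. The sample-size figure reproduces and is not in question.

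**2. Mix of the first 60.** The Discussion places the 60-participant analysis in the future, with 54 exposed already enrolled. If 60 counts all participants, the exposed share is at least 54/60 = 90%. As a cross-check by accrual rate: 54/14 = 3.86 exposed per month, so about 46 at month 12. If controls then accrue evenly (132 over the remaining 27 of 39 months, 4.9 per month), the total reaches 60 with about 52 exposed (87%). If 60 means exposed infants only, the first run could hold 60 exposed and no controls.

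**3. Run by exposure at the minimum sample.**

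| | Exposed | Unexposed |
|---|---|---|
| Early run | 54 | 6 |
| Later | 12 | 126 |
| Total | 66 | 132 |

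The early run holds 54/66 = 82% of the exposed and 6/132 = 5% of the unexposed, a difference of 0.773. The correlation is phi = (54 × 126 − 6 × 12) / √(60 × 138 × 66 × 132) = 0.79.

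**4. If run is ignored.** A run shift of s SD produces a spurious group difference of 0.773 × s. The documents give no run shift, so s is an assumption. The rates below are simulated for the t-test at one time point with all samples available; the noncentral t with noncentrality 0.773 × s × 6.633 agrees to within half a percentage point.

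| Assumed shift (SD) | Spurious difference (SD) | False positives, two-sided | False positives, one-sided |
|---|---|---|---|
| 0.1 | 0.08 | 8% | 13% |
| 0.2 | 0.15 | 17% | 26–27% |
| 0.3 | 0.23 | 33% | 45% |

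The nominal rate is 5%. The one-sided column assumes a shift in the hypothesised direction.

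**5. If run is adjusted for.** The variance of the group effect is inflated by 1/(1 − phi²) = 1/(1 − 0.628) = 2.69. The noncentrality falls to 0.5 × √(44/2.69) = 2.02 on 195 degrees of freedom, and power falls from 0.952 to 0.64.

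**6. Sensitivity to the early mix and the final size.** All rows below are at the planned d = 0.5.

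| Early run | Final sample | phi | Run-adjusted power | Two-sided false positives at 0.2 / 0.3 SD, unadjusted |
|---|---|---|---|---|
| 60 + 0 | 66 + 132 | 0.93 | 0.33 | 22% / 43% |
| 52 + 8 | 66 + 132 | 0.75 | 0.71 | 16% / 30% |
| 46 + 14 | 66 + 132 | 0.61 | 0.84 | 12% / 21% |
| 54 + 6 | 100 + 200 | 0.60 | 0.95 | 13% / 24% |
| 54 + 6 | 150 + 300 | 0.47 | 0.997 | 10% / 17% |
| 20 + 40 | 66 + 132 | 0 | 0.95 | 5% / 5% |

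The last row shows that the problem lies in the imbalance of an early run. An early run at the planned ratio would not confound run with exposure.

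**The case against.** The article never says that the preliminary values enter the final analysis. The early run might be a pilot, with everything measured again at the end. That would remove the run confounding, but only by thawing mostly exposed tubes a second time, because no aliquots exist. The documents give no stability data, so the size of that effect is unknown.

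It is also fair that 198 is a minimum. If recruitment goes well beyond it, adjustment for run costs little power, as the last table shows; the unadjusted comparison stays biased. Section 2.6 promises batch analysis and not literally one run, so several plates may be needed in any case. Plate layout is normally laboratory-manual detail, and its absence from an article is no fault. What stands is that the article states two incompatible assay times, one of which is unbalanced by its own recruitment figures.

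Several stronger readings are tempting but unsupported:

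- **Complete separation.** Putting all 66 exposed on one set of plates and all 132 controls on another would give two-sided rates of 10%, 26% and 51% at 0.1, 0.2 and 0.3 SD. A first run of 60 does not produce that split.
- **Beyond repair.** On the plain reading run and exposure do not coincide, so a model with a run term can be fitted, at the power cost shown.
- **Type I error spent by an interim look.** The Discussion states no interim group test, stopping rule or claim of success. A calculation at 60/198 of the information would also need the planned 2:1 mix, which the recruitment figures contradict.
- **Influence on clinicians.** The documents describe no route from interim biomarker results to RDS diagnosis or surfactant decisions, and section 2.6 withholds the biomarker identities until the findings are published.

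**Conclusion.** The point holds. Section 2.6 and the Discussion conflict on when study serum is assayed, and the undefined trigger in section 4 does not settle it. On the plain reading an early run would be at least 90% exposed. If its values are kept, confounding of run with exposure is strong but not total. The choice at the minimum sample is then between a false-positive rate of about 8% to 33% two-sided, for assumed shifts of 0.1 to 0.3 SD, and run-adjusted power of about 0.64 where 0.952 was planned. If the tubes are re-assayed, a differential freeze-thaw effect of unknown size takes the place of the run shift.

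This rests on three assumptions: that 60 counts all participants, that few controls are enrolled when the trigger is reached, and that the run shift is of the assumed size. The contradiction itself rests on none of them. It should be resolved before any study tube is thawed, because that step cannot be undone.

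**What to change.** Reconcile section 2.6, the Discussion and section 4 around one assay schedule:

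- Remove the assay of study samples at 60 participants, and bring the statement on preliminary results in section 4 into line.
- Keep every study tube unthawed until the end-of-recruitment batch analysis that section 2.6 already describes.
- Assay each exposed infant and its matched controls on the same plate, with all markers measured in one thaw, and include plate in the biomarker model.
- Do not begin aliquoting for new samples only, since handling would then differ by group.
- If pilot data are wanted, use sera from outside the study set.

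An interim set balanced at the planned ratio (for example 20 exposed and 40 controls) with bridging controls and a run term would also avoid the run confounding. It needs separate aliquots, which this study does not have, so waiting is the cleaner route.

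The cost is protocol wording and a plate map; the interim conference presentation is delayed or lost.
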